## Abstract

**Background:**

Veterans face an increased risk of common mental disorders when compared to civilian groups. However, veteran disengagement from treatment is a concern among health care providers, resulting in a need to explore novel ways of managing veteran mental health. Wearable devices, such as fitness trackers and smartwatches, have been explored for their potential to assess, monitor, and predict mental health outcomes in the general population. Such devices provide continuous data on metrics including physical activity, heart rate, sleep quality, and stress levels, offering a comprehensive view of the lifestyle and physiological factors influencing mental health.

**Objective:**

This study aims to explore the feasibility of using wearable technology as a data collection and potential health monitoring tool among UK veterans. It also aims to explore the associations between mental health, physical activity, and functioning factors among UK veterans.

**Methods:**

This is an observational feasibility study measuring mental health via validated questionnaires completed at baseline (T0), day 28 (T1), day 56 (T2), and day 84 (T3), and physiological metrics measured continuously via wrist-worn fitness trackers (Garmin vívosmart-5 watches) over 3 months (84 days). UK veterans will be recruited through convenience sampling methods. Statistical analysis will be exploratory, and machine learning models will be trained to detect changes in mental health and well-being outcomes.

**Results:**

Data collection was conducted between February 2025 and October 2025, and data analysis is scheduled to begin in January 2026.

**Conclusions:**

This study will provide information on the feasibility of using wearable technology devices within a UK veteran population and may inform potential future interventions seeking to integrate wearable-derived data alongside the management of common mental disorders in veterans experiencing mental health difficulties. Findings would also enhance understanding of the relationship between mental health and physiological factors (eg, physical activity and sleep) in UK veterans.

**International Registered Report Identifier (IRRID):**

PRR1-10.2196/73060

## Introduction

Veterans face an increased risk of common mental disorders (CMDs), with depression rates estimated to be approximately double that of the general population (40%) [1]. In the United Kingdom, a veteran is defined as an individual who has completed a minimum of 1 day’s paid employment in the Armed Forces [2]. There are estimated to be 2.03 million Armed Forces veterans in Great Britain [3,4], with additional numbers in Northern Ireland estimated between 40,000 and 60,000 [5].

While most veterans have positive in-service experiences, for some, their time in the military may lead to adverse mental health outcomes. Unique military occupational demands mean veterans may encounter stressors not experienced by civilian populations, such as combat exposure [6], which has been associated with an increased risk of experiencing adverse mental health outcomes, including posttraumatic stress disorder (PTSD) and depression [7].

The impact of depression, for instance, extends beyond mental health, increasing the risk of physical health problems such as type 2 diabetes and cardiovascular disease [8], as well as mental health comorbidities including PTSD, anger, anxiety, and alcohol misuse [9]. Further, the economic cost of depression in the United Kingdom is substantial, estimated as 5% of the country’s GDP [10]. In a sample of 693 veterans identified from clinical databases and accessing secondary mental health services in the United Kingdom, the rate of depression was identified as 22.9% [11]. Additionally, in a sample of UK veterans experiencing mental health difficulties who were deployed during the Iraq and Afghanistan conflicts, CMDs were identified as the most prevalent mental health problem (27.8%), followed by probable PTSD (9.4%) and alcohol misuse (8.4%) [12]. However, veteran disengagement from available treatment is a concern among mental health service providers, with many veterans either not seeking or discontinuing treatment early [13]. The need to explore novel ways of managing mental health difficulties in this population is clear.

Wearable devices, such as fitness trackers and smartwatches, have been explored for their potential to assess, monitor, and predict depression in patients [14,15]. Such devices can provide continuous data on an individual’s physical activity, heart rate, sleep quality, and stress levels, offering a comprehensive view of the lifestyle and physiological factors potentially influencing mental health. Wrist-worn devices are nondistracting and easy to administer to participants. They have been proposed as an effective way of collecting data in real time and have been successfully used to explore the association between depressive symptoms and wearable-derived features such as heart rate variability (HRV) [16], sleep, and physical activity in civilian samples [17]. Research investigating the relationship between mental health and features measurable via wearable technology devices is increasing, and health care providers are becoming increasingly focused on the potential use of wearable technology as a tool for health monitoring in the general population [18].

Military health research specifically has demonstrated the feasibility and acceptability of technology-driven methods in the management of veteran health, which offer a promising avenue for future interventions. For example, the successful use of a mobile app designed to manage harmful drinking behaviors demonstrates the potential of such interventions [19]. Real-time symptom monitoring and novel diagnostic and treatment approaches, such as behavioral activation through physical activity, could be key in the management of veteran mental health; however, there is limited research currently available within veteran groups exploring this [18]. As such, this study will use wearable technology (Garmin watches, vívosmart-5 model) to observe the relationship between mental health, physical activity, and functioning factors such as sleep among a UK veteran sample. Findings from this study may inform potential future interventions seeking to integrate wearable device data alongside the management of CMDs in veterans experiencing mental health difficulties.

This study aims to explore the associations between CMDs, including symptoms of anxiety and depression measured monthly using the 12-item General Health Questionnaire (GHQ-12), and indicators of physical activity recorded by wrist-worn fitness trackers among UK veterans. Garmin-derived metrics include steps, active minutes per day, HRV, stress levels, and overall activity patterns. In addition, the study seeks to examine the relationship between mental health and broader functioning factors, such as somatic symptoms, loneliness, and sleep, in relation to physical activation metrics (steps, active minutes per day, HRV, stress, and activity) obtained from fitness trackers. The primary outcome of interest is the change in GHQ-12 score from baseline (T0) to day 84 (T3) associated with the change in physical activity over the 3-month study period. The study also aims to assess the feasibility of using fitness trackers to enhance the prediction and management of CMDs among UK veteran populations, to inform the development of a potentially larger-scale initiative. Feasibility will be assessed through recruitment rate, retention rate, and data completeness of both watch-derived data and monthly questionnaire responses. By integrating objective physiological data with self-reported mental health measures, this work ultimately aims to support improved monitoring and intervention strategies for CMDs within the veteran population.

## Methods

### Ethical Considerations

#### Ethics Approval

The study protocol and all related research material (informed consent forms, participant information sheet, recruitment materials, and assessments) were reviewed and approved by the King’s College London Research Ethics Committee (reference number MRA-24/25-45701) via a minimal risk self-registration process, in line with King’s College Research Ethics Committee minimal risk guiding principles.

#### Privacy and Confidentiality

The study will collect limited personally identifiable information (name, contact details, service number verification, address, and study entry date) solely for participant communication and study administration. Identifiable data will be held securely by King’s College London and Combat Stress, stored separately from the research dataset, with access restricted to authorized members of the research team as approved by the principal investigator. Personally identifiable information will be held for a period of up to 1 year after the study has been completed. All data processing will comply with the General Data Protection Regulation (GDPR; specifically, the GDPR 2018 Act of Parliament) and institutional data–governance policies. Wearable-derived data will be transferred from the Garmin Connect app to SyncRation, the approved secure research platform used at King’s College London, via encrypted protocols (Transport Layer Security/Secure Sockets Layer) and stored on access-controlled servers with encryption at rest. Systems used by the research team maintain audit logs of data access and changes, and operate within protected, segmented network environments to reduce security risk. Identifiable information is stored separately from research datasets, with linkage performed through pseudonymized study identifiers. Garmin does not have access to any identifiable research data. Nonidentifiable information will be held for a period of up to 7 years after the study has been completed (Figure 1).

**Figure 1 figure1:**
[figure not shown]
Data flow of wearable-derived data. PI: principal investigator; SSL: Secure Sockets Layer; TLS: Transport Layer Security.

#### Informed Consent Procedures

If the participant agrees to take part, informed consent will be obtained at the end of the online screening questionnaire before the collection of any data. Participants will be informed that they can withdraw from the study at any time. All data, including those from withdrawn participants, except for those who request that their data be deleted/not used, will be included in the final analysis.

#### Compensation

Participants will be gifted a £10 (US $13.40) Amazon voucher upon completion of the study. They will also be gifted the Garmin vívosmart-5 watch used to collect study data free of charge; the watch is valued at £129.99 (US $174.19).

### Eligibility Criteria

Participants will be veterans of the UK Armed Forces who meet caseness for CMDs, including symptoms of anxiety and depression, defined by a cutoff score of ≥12 on the GHQ-12. A brief online survey will screen for study inclusion criteria and obtain informed consent from participants (Textbox 1). Eligible participants will receive a phone call from a member of the research team to confirm their delivery address for the Garmin watch, their status as a veteran via their service number, and their service history (when they served and when they left service).

Participant eligibility criteria.
**Inclusion criteria**
UK military veterans aged ≥18 years. In the United Kingdom, individuals are defined as veterans if they have completed a minimum of 1 day of paid employment in the UK Armed Forces [20]Self-reported experiences of common mental disorders, including symptoms of anxiety or depression, caseness identified by a score of ≥12 on the 12-item General Health Questionnaire [21]Fluent (speaking and reading) in EnglishUse an iOS or Android device released within the previous 5 yearsAccess to a USB-C compatible charging port
**Exclusion criteria**
Living outside of the United KingdomCurrently servingUnwilling and/or unable to provide informed consent

### Study Design

An observational feasibility study in which 50 UK veterans who self-report experiencing CMDs, including symptoms of anxiety and depression, will be recruited through convenience sampling methods. The target population for this study is not clinical, and there are no comparators. Participants will wear a Garmin watch, delivered to their home address, for 84 days, and complete baseline measures plus 3 monthly questionnaires about their mental health and well-being, administered on Qualtrics survey software (Qualtrics Labs, Inc). Participants will wear the devices in their everyday environment and will be sent automated email reminders to complete the monthly surveys.

Participant self-reported mental health and well-being data will be collected via monthly online questionnaires (a summary of the measures used is detailed in Table 1), and behavioral and physiological indices will be measured and collected using Garmin watches (vívosmart-5 model; Figure 2). Data will be collected via the watches on the following outcomes continuously (24/7): activity level (number of steps, active minutes, and self-reported activity), HRV, overall body battery, sleep (sleep quality, sleep score, and hours of sleep), and stress.

**Table 1 table1:** Mental health and well-being measures.

Mental health and well-being measures	Description of measure	Cutoff
Alcohol Use Disorders Identification Test for Consumption [22]	3-item measure of heavy drinking and/or active alcohol dependence. Assesses frequency and quantity of alcohol consumption, and frequency of high-intensity drinking episodes (≥6 units for women, ≥8 for men).	Scores range from 0 to 12. ≥5 indicates a positive screen. Categories: low risk (0-4), increasing risk (5-7), higher risk (8-10), and possible dependence (11-12).
12-item General Health Questionnaire [21]	Measure of common mental disorders, focusing on non-psychotic symptoms such as depression and anxiety.	Scores range from 0 to 36 (Likert scale). Caseness is defined as ≥12.
Generalized Anxiety Disorder-7 [23]	Screens for and assesses the severity of generalized anxiety disorder.	Scores range from 0 to 21. Categories: minimal (0-4), mild (5-9), moderate (10-14), and severe (15-21).
Patient Health Questionnaire-2 [24]	Brief screening tool for depression assessing frequency of low mood and anhedonia over the past 2 weeks.	Scores range from 0 to 6. ≥3 indicates probable depression.
Patient Health Questionnaire-15 [25]	Measures the severity of somatic (physical) symptoms such as pain and fatigue.	Scores range from 0 to 30. Categories: minimal (0-4), low (5-9), medium (10-14), and high (15-30).
Posttraumatic Stress Disorder Checklist-5 [26]	Assesses presence and severity of PTSD^a^ symptoms aligned with DSM-5 criteria; used for screening and monitoring over time.	Scores range from 0 to 80. ≥31 indicates provisional PTSD diagnosis.
Pittsburgh Sleep Quality Index [27]	Assesses sleep quality and disturbances over a 1-month period.	Scores range from 0 to 21. ≥5 indicates significant sleep disturbance.
UCLA^b^ Loneliness Scale-3 [28]	Brief 3-item measure of perceived loneliness.	Scores range from 3 to 9. Categories: not lonely (3-5) and lonely (6-9).
Warwick-Edinburgh Mental Well-being Scale-7 [29]	Measures positive mental well-being, including aspects such as personal growth, autonomy, and relationships; shortened 7-item version.	Scores range from 7 to 35. Categorized using ±1 SD as low, normal, or high well-being.
Dimensions of Anger Reactions-5 [30]	Brief standardized measure of trait anger; sensitive screening tool for anger-related difficulties.	Scores range from 5 to 25. ≥12 indicates problematic anger.
Insomnia Severity Index [31]	Brief screening tool measuring the severity of insomnia symptoms.	Scores range from 0 to 28. Categories: none (0-7), subthreshold (8-14), moderate (15-21), and severe (22-28).
International Physical Activity Questionnaire Short Form [32]	Assesses physical activity across vigorous, moderate, walking, and sitting domains over the past 7 days.	Produces MET^c^-min/week. Categories: low, moderate, high physical activity.
Perceived Stress Scale-10 [33]	Measures perceived stress based on feelings of unpredictability, uncontrollability, and overload over the past month.	Scores range from 0 to 40. Categories: low (0-13), moderate (14-26), and high (27-40).

^a^PTSD: posttraumatic stress disorder.

^b^UCLA: University of California, Los Angeles.

^c^MET: metabolic equivalent of task.

**Figure 2 figure2:**
[figure not shown]
Sample devices (Black).

A pilot study, with 5 participants, will be conducted prior to commencing the study. The pilot study will be conducted for the purpose of testing the study design and study schedule. The pilot study sample is made up of experts working in the field of military mental health who have experience working with the veteran population. Feedback from the pilot study will be used solely to inform the main study design and study schedule; any alterations identified from the pilot study will be made before the main study commences. Data collected from the pilot study will not be used in the analysis of results from the main cohort.

### Study Schedule

A recruitment advert will include a link to the registration survey where participants can register their interest in taking part in the study. This survey will collect participants’ consent to be contacted about the study, contact details, and a copy of the participant information sheet will be included, and informed consent to participate in the study will be collected. Prospective participants will confirm they meet the inclusion and exclusion criteria on this survey. Those who do not meet the inclusion criteria for the study will be informed via email. Eligible participants will be invited to attend an online verification call conducted with a member of the research team. During this call, participants will be given the opportunity to ask any questions they may have about the study, go through the participant information sheet, and confirm their home delivery address for the Garmin watch. The following questions will be asked to confirm participants’ status as a veteran and service history: (1) “Please could you tell me how long you served for?” (2) “And please confirm that you are no longer serving?” (3) “Please could you provide your service number?” and (4) “Please could you tell me a little bit about your time in service? Your role and responsibilities, for example. Just briefly.” Eligible participants who wish to participate in the study will be emailed a copy of the participant information sheet for their own records.

Garmin watches will be posted to participants’ home addresses; participants will be emailed by the research team that the watch is on its way to ensure successful delivery. A video call with a member of the research team will be conducted to support the setup of the device if participants require assistance. Following delivery of the watch, an account will be set up for participants on the SyncRation platform by a member of the research team. Automated emails will be sent from SyncRation to participants’ personal emails throughout the study. A SyncRation automated email (Table 2, SyncRation email 1) will include a link to a document containing participant instructions for setting up the watch and the Garmin Connect app, plus a link to synchronize participants’ Garmin Connect app with the SyncRation portal. This will include consent for the research team to access the participants’ Garmin data via SyncRation. Participants will be requested to begin wearing their watch after they have successfully set up their watch with the Garmin Connect app and consented to the study team accessing their data via the SyncRation platform, to ensure comfort and fit of the device. The research team will be contactable via email to address any technical difficulties throughout the study period.

**Table 2 table2:** Study flowchart—participant journey.

Study phase and activity			Weeks																								
			0		1		2		3		4		5		6		7		8		9		10		11		12
**Recruitment^a^**																											
	Recruitment (Facebook, LinkedIn, veteran groups, or newsletters)																										
	Registration survey: online eligibility screen; contact details: name, email, and phone number; consent to be contacted; participant information sheet; and informed consent.																										
**Onboarding**																											
	Study explanation (verification call)	×																									
	Address confirmed for Garmin delivery (verification call)	×																									
	Veteran status confirmed (verification call)	×																									
	Service history details (verification call)	×																									
	Participant information sheet copy (emailed)	×																									
	Garmin sent to participant’s home address	×																									
	Watch on its way (emailed)	×																									
	Watch and Garmin Connect app setup instructions; Garmin Connect app—SyncRation synchronization link; consent for research team to access data via SyncRation (SyncRation email 1)	×																									
	Baseline measures questionnaire (SyncRation email 2)	×																									
	Optional video call to support setup	×																									
	Day 1—study commencement (emailed)			×																							
**Baseline data**																											
	Sociodemographics	×																									
	International Physical Activity Questionnaire Short Form	×																									
	BMI	×																									
	Dimensions of Anger Reactions-5	×																									
	Insomnia Severity Scale	×																									
	Perceived Stress Scale-10	×																									
**Monthly Mental Health Questionnaire (to be completed every 28 days)**																											
	Alcohol Use Disorders Identification Test for Consumption	×								×								×								×	
	General Health Questionnaire-12	×								×								×								×	
	Generalized Anxiety Disorder Scale-7	×								×								×								×	
	Patient Health Questionnaire-2	×								×								×								×	
	Patient Health Questionnaire-15	×								×								×								×	
	Posttraumatic Stress Disorder checklist for DSM-5^b^	×								×								×								×	
	Pittsburgh Sleep Quality Index	×								×								×								×	
	UCLA^c^ Loneliness Scale-3	×								×								×								×	
	Short Warwick-Edinburgh Mental Well-Being Scale-7	×								×								×								×	
**Fitness tracker**																											
	Sleep: sleep score, sleep hours, and sleep quality			—^d^		—		—		—		—		—		—		—		—		—		—		—	
	HRV^e^ morning and evening			—		—		—		—		—		—		—		—		—		—		—		—	
	Activity: steps, active minutes, and self-reported activity			—		—		—		—		—		—		—		—		—		—		—		—	
	Stress			—		—		—		—		—		—		—		—		—		—		—		—	
	Body battery			—		—		—		—		—		—		—		—		—		—		—		—	
**Questionnaire reminder emails**																											
	MH^f^ Questionnaire link (SyncRation email 3)									×																	
	MH Questionnaire link (SyncRation email 4)																	×									
	MH Questionnaire link + final measures survey (SyncRation email 5)																									×	
**Final measures**																											
	Weight	×																								×	
	Perceived Stress Scale-10	×																								×	
	Insomnia Severity Scale	×																								×	
	Dimensions of Anger Reactions-5	×																								×	
	International Physical Activity Questionnaire Short Form	×																								×	
**Incentive to complete the final questionnaire**																											
	Thank you, plus instructions to unlink Garmin Connect from SyncRation (emailed)																									×	
	£10^g^ Amazon voucher (emailed)																									×	

^a^Recruitment will occur prestudy.

^b^DSM-5: Diagnostic and Statistical Manual of Mental Disorders, Fifth Edition.

^c^UCLA: University of California, Los Angeles.

^d^Continuous data collection from week 1 to week 12.

^e^HRV: heart rate variability.

^f^MH: mental health.

^g^£10=US $13.40.

A link to the baseline measurement questionnaire will be sent to the participants (Table 2, SyncRation email 2). This will include basic demographic information, weight, height, as well as psychometric measures of mental and physical health outcomes. Once the baseline questionnaire is complete, the following day will signify the start date of the study for the participant (Day 1). Participants will complete all monthly questionnaires about their mental and physical health via the online survey platform (Qualtrics). This survey link will be automatically emailed to participants on day 28 (T1), day 56 (T2), and day 84 (T3) of the study via SyncRation. All physiological study data will be collected automatically from the watch, via the Garmin Connect smartphone app. Participants will be emailed 2 reminders to complete each survey: 2 days and 1 week after the survey is first emailed. If the questionnaires remain uncompleted, participants will be called by the research team a further 2 times, 8 days and 10 days after the date the survey link was emailed. Those who still do not complete the survey will be emailed a final time to say they have been withdrawn from the study. Participants who do not complete the questionnaires will not receive the £10 (US $13.40) Amazon gift voucher, but they may opt to keep the Garmin watch. Participants who complete the questionnaires will be gifted their watch after study completion and will receive a £10 (US $13.40) Amazon voucher as a gesture of goodwill for taking part. Participants will be sent a thank-you email for their participation, which will include instructions for unlinking their Garmin Connect app from the SyncRation platform. Participants who do not unlink from SyncRation will be manually unlinked by a member of the research team through the SyncRation platform to ensure cessation of data collection beyond the study end date.

Watches will be delivered to participants’ home addresses and posted in batches. Due to the geographical distribution of participants across the United Kingdom, devices will be received and set up at different time points, resulting in variation in individual study commencement dates (day 1). Study commencement is defined as the point at which the watch is successfully set up and linked to the SyncRation platform and baseline measures are completed. Following successful setup of the device and completion of the baseline questionnaire, participants will be emailed by the research team to mark the study commencement (day 1), and all participants will complete the same study schedule. The study schedule is illustrated in Table 2, which includes all data collection points and questionnaire measures. A selection of health and well-being questionnaires has been selected to enable assessment of participants' mental health and well-being. See Multimedia Appendix 1 for full questionnaire markup.

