### Sample Size

This study is an observational feasibility study. As such, no power calculation has been performed. Research specifically within the UK veteran populations is limited; a sample of 30 was used in a feasibility study using wearable technology to predict PTSD symptoms and cannabis use among UK veterans [36]. Feasibility trials using wearable devices in community and veteran populations commonly recruit between 15 and 110 participants [37-39], and a recent US veteran wearable feasibility study successfully used a sample of 74 [40]. The selected sample size for this study is 50 veterans. A sample of 50 enables the study to estimate key feasibility outcomes, such as recruitment rate, retention, survey completion, and wearable data availability, with acceptable precision for planning a larger study. Although the machine learning (ML) component is exploratory, each participant contributes up to 84 days of continuous data, providing a significant amount of data [40]. In feasibility settings, ML analysis focuses on identifying whether wearable features show consistent signals and whether models can be trained without substantial overfitting, rather than producing validated prediction models.

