### Adverse Events

Participation in this study is not expected to result in adverse events. Nevertheless, researchers will monitor changes in participants' mental health over the course of the study to ensure safety. Incoming GHQ-12 scores from participants' monthly surveys will be monitored on a weekly basis by the research team. Weekly monitoring will be conducted to account for participants’ different start dates and, therefore, different monthly questionnaire completion dates between participants, to ensure that safeguarding response procedures are initiated within a week of data collection. Any participants reporting an increase in GHQ-12 score of ≥15 points between 2 consecutive surveys will be contacted immediately by a member of the research team. During this contact, participants will be provided with the signposting booklet of veterans’ mental health services. If concerns about the participant’s well-being arise during this correspondence, the case will be escalated for further assessment. This will involve a call with a designated member of the research team. Further action required following confirmation of risk will result in a referral to the clinical lead (DM) to perform a clinical interview and risk assessment, and to determine whether and what additional support is required and whether the participant should be withdrawn from the study. All contact, assessments, and actions undertaken in response to potential adverse events will be documented, and any data collected before withdrawal will be used for analysis.

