#### Descriptive and Feasibility Analyses

Baseline characteristics will be summarized using standard descriptive statistics. Questionnaire outcomes will be described at T0, T1, T2, and T3. Feasibility outcomes (recruitment rate, retention, questionnaire completion, proportion of valid wear days and weeks, and completeness of each wearable stream) will be reported using counts, percentages, medians, and IQRs as appropriate. Participants will be grouped into quartiles of data completeness to assess engagement patterns as undertaken in prior work [40,41].

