#### Exploratory Modelling

The primary exploratory outcome is the change in GHQ-12 score from T0 to T3. Secondary outcomes include change in other questionnaire scores. Initial associations between wearable features and mental health outcomes will be examined using simple regression models to estimate effect sizes.

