## Results

Enrollment for the pilot phase was completed in December 2024, with all pilot study participants completing the study (n=5). Data collection for the main study commenced in February 2025 and concluded in October 2025. As of March 2026, 52 participants have been recruited, of whom 48 have completed the study procedure, and 4 have withdrawn from the study. Recruitment occurred between February 2025 and August 2025. Data analysis is scheduled to begin in January 2026, with results expected to be submitted for publication in May 2026.

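### Withdrawing participants who leave a monthly survey unanswered forecloses their T3 GHQ-12 score, hides skip-then-return non-response and leaves the retention figure ambiguous (minor)

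*Protocol article*

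**What the plan says.** The Study Schedule section (text after Table 2) sends survey links on days 28, 56 and 84. The follow-up procedure applies to every survey: "Participants will be emailed 2 reminders to complete each survey: 2 days and 1 week after the survey is first emailed". Two calls follow, 8 and 10 days after the link. The consequence of continued silence is stated: "Those who still do not complete the survey will be emailed a final time to say they have been withdrawn from the study". No exception, route back in or continued follow-up is described.

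Four other places bear on this rule:

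- Descriptive and Feasibility Analyses lists retention and completion as separate results: "Feasibility outcomes (recruitment rate, retention, questionnaire completion, proportion of valid wear days and weeks, and completeness of each wearable stream". Sample Size gives this as a purpose of recruiting 50 veterans: "estimate key feasibility outcomes, such as recruitment rate, retention, survey completion, and wearable data availability, with acceptable precision for planning a larger study".
- Exploratory Modelling: "The primary exploratory outcome is the change in GHQ-12 score from T0 to T3".
- Informed Consent Procedures brings into the final analysis "All data, including those from withdrawn participants", unless the person asks for deletion.
- Adverse Events sets the safety trigger at "an increase in GHQ-12 score of ≥15 points between 2 consecutive surveys".

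Results reports 52 recruited, "of whom 48 have completed the study procedure, and 4 have withdrawn from the study".

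**The concern.** The rule turns non-response to one survey into exit from the study. The T0-to-T3 change needs only the first and last scores, so a gap at T1 or T2 need not cost the outcome, but under this rule it does. Keeping withdrawn participants' data does not help, because a T3 score that was never requested does not exist.

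The Overview of the Statistical Analysis section makes data availability, engagement and retention primary analytic aims, intended to inform a larger study. That study needs to know how many people leave by choice and how many skip a survey and come back. The rule prevents the second from being seen, and its withdrawals may be counted together with the first. The larger study could then plan for the wrong kind of loss.

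**Working it through.** **1. Reported disposition.** 48 + 4 = 52, so the figures agree. Retention as recorded is 48/52 = 92.3% (Wilson 95% CI 81.8% to 97.0%; exact interval 81.5% to 97.9%). Withdrawal is 4/52 = 7.7%.

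**2. What the rule removes, by survey missed.** This assumes that withdrawal stops later surveys and that the person would have answered them.

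| Survey missed | Later GHQ-12 scores removed | Safety comparisons left under the rule | Comparisons if kept in: adjacent planned surveys / consecutive completed surveys | Removed by the rule |
|---|---|---|---|---|
| T1 | 2 (T2, T3) | 0 | 1 (T2–T3) / 2 (T0–T2, T2–T3) | 1 / 2 |
| T2 | 1 (T3) | 1 (T0–T1) | 1 (T0–T1) / 2 (T0–T1, T1–T3) | 0 / 1 |
| T3 | 0 | 2 (T0–T1, T1–T2) | 2 / 2 | 0 |

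**3. Range for retention.** Let r, from 0 to 4, be the number of the 4 withdrawals made by the rule. If those r people are not counted as lost, retention is (48 + r)/52. That runs from 48/52 = 92.3% (r = 0) to 52/52 = 100% (r = 4; Wilson 95% CI 93.1% to 100%). In planning terms, 100 × 52/48 = 108 recruits per 100 retained, against 100. Sampling error alone on 48/52 gives 100/0.970 = 103 to 100/0.818 = 122, a width of 19 recruits against a shift of at most 8.

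**4. Illustration for a larger study.** The article gives no non-response rate, so let m be an assumed chance of leaving any one survey unanswered after all contacts, equal and independent at T1, T2 and T3. Expected T3 scores are n(1 − m) if people stay in and n(1 − m)³ under the rule. With n = 50:

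| m | Stay in | Under the rule | Lost to the rule |
|---|---|---|---|
| 2% | 49.0 | 47.1 | 1.9 |
| 5% | 47.5 | 42.9 | 4.6 |
| 10% | 45.0 | 36.5 | 8.5 |
| 15% | 42.5 | 30.7 | 11.8 |

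**5. Where this study sits on that scale.** If all 4 withdrawals came from the rule, (1 − m)³ = 48/52, so m = 1 − 0.9231^(1/3) = 2.6%. The T3 scores lost to the rule would then be about 52 × 0.974 − 48 = 2.6. The rows at 5% and above therefore show what the rule could cost elsewhere, not what it cost here.

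**The case against.** The strongest defence is operational. A person reaches withdrawal only after the original email, two reminders and two calls, and someone silent through five contacts can fairly be classed as lost to follow-up. Nothing in the article shows that such people would have answered later. This stands, and it is why the loss of T3 scores is conditional. It does not answer the point that the rule prevents anyone from finding out.

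A reader might infer more than the document supports in five ways:

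- *Completion is 100% by construction.* This is true only among retained participants. The article does not fix that denominator. Completion over all starters stays informative, and withdrawal by request or clinical decision also separates the two outcomes. Only skip-then-return patterns are truly hidden.
- *Safety monitoring is undermined.* At most 1 to 2 comparisons go after a missed T1 and 0 to 1 after a missed T2. If consecutive means adjacent planned surveys, a missed T2 already breaks both pairs that contain it and the rule removes nothing further. The two calls also give some contact.
- *48 + 4 = 52 shows there were no partial completers.* A completed/withdrawn split would normally sum to the total under any rule, and someone withdrawn after answering T1 is a partial completer.
- *Watch data stop at withdrawal too.* The article does not say so. It mentions unlinking only in connection with the end of the study.
- *Retention by choice was really 100%.* That is the upper bound, reached only if all 4 withdrawals came from the rule.

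It is also fair that all analyses are declared exploratory and that collection has ended, so the rule cannot be changed for this cohort.

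**Conclusion.** The point holds as a minor design concern. The article states the rule outright, so this is not a detail left to an unseen analysis plan, and no analysis can recover a survey that was not sent. A missed T1 or T2 forecloses the T3 GHQ-12 score, intermittent non-response cannot be observed, and the recorded 92.3% may combine voluntary and administrative exits.

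The size here is bounded at 4 of 52 participants, with retention by choice or clinical decision somewhere between 92.3% and 100%. The effect on the safety trigger is slight.

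The conclusion assumes that withdrawal ends later survey emails, which is the plain reading but is not spelled out. How the 4 withdrawals arose, which surveys they missed and whether all 4 had started are not stated, so the actual effect could be anything from nothing to that bound.

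**What to change.** **This study (reporting only).**

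- Classify the 4 withdrawals by route: non-response rule, own request or clinical decision.
- Report T1, T2 and T3 completion separately, each over all participants who started.
- Report retention twice: as recorded, and with rule-based withdrawals not counted as losses.
- State that the rule prevents intermittent non-response from being seen.

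This needs one small table and a sentence or two, from records the team should already hold.

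**Before the rule is carried into a larger study.** Record an unanswered survey as missing, still send the next scheduled one, and withdraw only on request or clinical decision. This adds no new measures. The cost is a few further emails and calls to people who may not reply, and some T3 scores from participants with a gap earlier on.
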